## Abstract

**Background:**

The post marketing safety surveillance program for a drug containing a new chemical entity should assess both, the safety outcomes that relate specifically to the targeted population, as well as those that could potentially be related to special pharmacological characteristics of the drug. Active safety surveillance using valid epidemiological study designs has been proven to be a pertinent and reliable method to approach this endeavor.

**Methods/design:**

The primary objective of the study is to compare incidence rates of serious adverse events in users of all types of newly prescribed oral HRT products. This active surveillance study will assess pertinent cardiovascular outcomes - in particular venous and arterial thromboembolism - and other serious adverse events (SAEs) in new HRT users over a period of several years. One product under surveillance is Angeliq^®^, which contains the novel progestagen drospirenone (DRSP) combined with estradiol. In addition, all other oral combined HRT products with a novel progestagen or estrogen that will be newly marketed during the study period will be studied. These new HRT products will be compared with established HRT products. The combined cohort will include at least 30,000 women recruited in several European countries. At least 90,000 years of observation are expected from the field work which started in early 2002 and will end around 2008. The participating women will complete a baseline survey using a self-administered questionnaire to describe the baseline risk. After 6 months, 12 months, and then on an annual basis, they will fill out a questionnaire in which they record complaints and events during the use of the prescribed HRTs. All adverse outcomes occurring during the observational period will be evaluated.

**Discussion:**

A complete lifetime medical history, individually validated SAEs over time, and a low loss to follow-up rate are essential for a robust safety assessment. Therefore, the lifetime history of diseases and relevant medications will be documented. Reported SAEs will be validated and analyzed. A four level, multi-faceted follow-up process was established to ensure low loss to follow-up rates (e.g., 3–5% after three years of follow up). Multivariate methods will be used to adjust for confounding.

## Background

The safety of a novel drug product containing a new chemical entity should be assessed in an extensive post marketing safety surveillance program. It is also prudent to assess both, the safety outcomes that relate specifically to the targeted population, as well as those that could potentially be related to the special pharmacological characteristics of the novel drug product. Differentiating between the inherent background population risk and a potential incremental risk due to treatment is often challenging. Active safety surveillance using valid epidemiological study designs has been proven to be a pertinent and reliable method to approach this endeavor.

Long-term active safety surveillance of new HRT products has gained particular importance following the intense scientific debate on the risk/benefit profile of HRT products after the publication of the WHI results [1]. The active safety surveillance study proposed in this protocol, the European Active Surveillance Study of Women taking HRT (EURAS-HRT) study, will assess the risk profile of marketed oral combined HRT products, by comparing HRT products that contain novel progestagens with older HRT products. The primary objective of the study is to compare incidence rates of serious adverse events - in particular cardiovascular outcomes - in new users of all types of oral HRT products. This large, multinational, prospective, controlled, non-interventional, long-term cohort study will follow a series of cohorts for a period of seven years. The study is sponsored by Schering AG with an unconditional grant. Study conduct and data analysis are carried out by an independent investigator under the stewardship of an international advisory committee.

One drug product under surveillance in the EURAS - HRT study is Angeliq^®^, which contains a novel synthetic progestagen drospirenone (DRSP) [2,3] combined with estradiol. In addition, all other oral combined HRT products with a novel progestagen or estrogen that will be newly marketed during the study period will be included in this study. These new HRT products will be compared with established HRT products.

As estrogen/progestagen combinations increase the risk for thrombembolism [4], all new drug products that contain a novel estrogen or progestagen should be investigated for their influence on venous and arterial thromboembolic events rates. A large, prospective, controlled cohort study of OC users (EURAS OC Study), which compared DRSP-containing OCs users with other OCs users, demonstrated that DRSP is not associated with an increased incidence for thromboembolic events in OC users [5]. However, because OC users are two to three decades younger than the typical HRT user the results of the OC study can only partially be extrapolated to older age groups.

Furthermore, given DRSP's antimineralocorticoide pharmacological characteristics, specific outcomes such as the risk of hyperkalemia and dysrhythmia, and subsequent serious cardiac problems will be assessed in this study. As secondary objective all other outcomes of the long-term observation will be evaluated.

A long-term observational cohort study, which compares rates of adverse events among users of Angeliq^® ^(and other new HRT products) with those among users of other marketed oral HRTs, is an appropriate design to assess long-term risks and benefits under real-life-conditions of drug utilization, i.e. taking into account all possible interactions with co-morbidity and co-treatment which are common in higher age groups. Potential differences between first-time users of an HRT product and users who switch from one preparation to another will be investigated. Moreover, the potential of greater risk during the early period of use (e.g. the first year) will be carefully monitored.

The pilot phase of this surveillance study was started in early 2002, using a cohort of women who visited European physicians who prescribe HRT. This revised protocol reflects the experiences gained in the pilot phase of the study. Further background information and details are available at the study's website [6].

## Methods/design

### Objectives

The study will monitor utilization practice with particular attention to long-term effects in user cohorts of: 1) Angeliq (and potentially of other novel oral continuous-combined HRT products); 2) other oral continuous-combined HRTs; and 3) other oral HRTs

under routine conditions, all of these in the medical practice of several European countries.

The study will compare incidence rates of serious or unexpected adverse events among users of the three above-mentioned HRT user cohorts to analyze the following:

- *Events that played a key role in earlier risk considerations*, such as myocardial infarction, stroke, sudden death, and venous thromboembolism;

- *Other medically significant events*.

The study is not designed to investigate long-term outcomes such as breast, colon, or endometrial cancer or osteoporotic fractures, on account of the expected small number of cases and relatively short treatment periods. However, all serious or unexpected outcomes will be fully documented, and evaluated. This means that significant adverse events will be analyzed under "real-life conditions", i.e. without influencing the prescription behavior of the physicians or the desires of the women. It is understood that HRTs will be prescribed according to international guidelines.

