### Design

Prospective, controlled cohort study of users of HRT with follow-up: one cohort of women starting with or switching to Angeliq^®^, one comparison cohort of other oral continuous-combined HRT users (starter or switcher), and a third cohort of all other marketed oral HRTs (starter or switcher).

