### Information gathered

#### Exposure data

Exposure is defined - for this surveillance study - as new use of any oral HRT. This includes women who are first time users (starters) or those who switch to a new brand. The exposure group of particular interest is the group using Angeliq^®^, and two other exposure groups (other oral continuous-combined HRT products and all other oral HRT products) have been defined as comparators (see above). Herbal menopausal drugs and SERMS will not be included in the main analysis.

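### Other novel HRT products belong to the index side in the Abstract, Background and (potentially) Objectives, but fall into the comparator cohorts as Design and Exposure data define them

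*Protocol article*

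**What the plan says.** The Protocol article describes the groups in several places.

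- **Abstract and Background.** The study covers Angeliq and, beyond it, "all other oral combined HRT products with a novel progestagen or estrogen that will be newly marketed during the study period will be included". The contrast is stated as "These new HRT products will be compared with established HRT products". A later paragraph of the Background again groups other new products with Angeliq.
- **Objectives.** The first cohort is "Angeliq (and potentially of other novel oral continuous-combined HRT products"). The other two are other oral continuous-combined HRTs and other oral HRTs.
- **Design.** The first cohort is "one cohort of women starting with or switching to Angeliq". The rest are "one comparison cohort of other oral continuous-combined HRT users (starter or switcher), and a third cohort of all other marketed oral HRTs".
- **Exposure data.** The index group is Angeliq alone: "The exposure group of particular interest is the group using Angeliq". For the reference side, this section states that "two other exposure groups (other oral continuous-combined HRT products and all other oral HRT products) have been defined as comparators".
- **Study size estimation.** A 10% market share is assumed for the new product or products; the wording leaves singular or plural open.
- **Final analysis.** The comparison is between the three main cohorts, and relative risks below 2.0 to 3.0 are to be treated as inconclusive.

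**The concern.** These sections do not describe the same three cohorts. Design and Exposure data define the comparators by the word other and exclude nothing on grounds of novelty. Read literally, a second novel continuous-combined product is a comparator in cohort 2. The Background makes the same product one of those under evaluation, and Objectives may put it in cohort 1. A novel product that is not continuous-combined is covered by the Background's promise, yet falls into cohort 3 under Objectives, Design and Exposure data alike.

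The reference group of the main contrast could therefore contain products whose safety the study is meant to assess. Under the Objectives reading, the Angeliq result could instead be averaged with that of other progestagens or estrogens.

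Recruitment is affected as well as analysis. Under Study participants, each woman prescribed the new HRT triggers selection of one woman from each of the other two groups. Whether a user of another novel product triggers that selection, or may herself be selected as a comparator, depends on the unresolved definition. Reclassifying women later cannot supply comparators who were never selected.

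**Working it through.** **1. Where a second novel product goes**

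| Section | Novel, continuous-combined | Novel, not continuous-combined |
|---|---|---|
| Abstract, Background | index side | index side |
| Objectives | cohort 1, potentially | cohort 3 |
| Design | cohort 2 | cohort 3 |
| Exposure data | comparator | comparator |

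No section reconciles the rows.

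**2. The plan's own figures**

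Inputs from Study size estimation: rate ratio 3.0, 80% power, 95% confidence (taken as two-sided), 10% share, MI rate 0.2%, VTE rate 0.3%. The Schoenfeld formula gives

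events = (1.96 + 0.842)² / (0.10 × 0.90 × (ln 3)²) = 72.3, rounded up to 73.

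Women-years = 73 / [rate × (0.9 + 0.1 × 3)]:

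- MI: 73 / (0.002 × 1.2) = 30,417 (stated 30,000)
- VTE: 73 / (0.003 × 1.2) = 20,278 (stated 20,000)

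Both reproduce, so 10% works as the index share. The cardiovascular mortality figure does not reproduce (73 / (0.005 × 1.2) = 12,167 against 44,000). That is a separate matter and is not used here.

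**3. Angeliq-only index, other novel products among the pooled comparators**

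Assumptions: the 10% covers all novel products, a fraction q of it is products other than Angeliq (the documents give no q), and every novel product has a true ratio of 3.0. The novel fraction of the comparator is f = 0.1q / [1 − 0.1(1 − q)], and the observed ratio is 3 / (1 − f + 3f).

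| q | f | Observed ratio | MI women-years needed | VTE women-years needed |
|---|---|---|---|---|
| 10% | 0.01/0.91 = 0.011 | 2.94 | 34,583 | 23,056 |
| 25% | 0.025/0.925 = 0.027 | 2.85 | 43,333 | 28,889 |
| 50% | 0.05/0.95 = 0.053 | 2.71 | 69,167 | 46,111 |

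All requirements stay below the planned 90,000. Much of the increase comes from the smaller Angeliq share, not from dilution. At q = 50%, the share alone raises the events needed from 73 to 7.85 / (0.05 × 0.95 × 1.207) = 137; dilution raises them further to 166. Power for MI at 90,000 women-years is still about 89%.

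If Angeliq has a true ratio of 1.0 and the others 3.0, the observed ratio is 1 / (1 + 2f) = 0.98, 0.95 and 0.90, which is slightly protective. If the others are at 1.0, there is no bias.

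**4. Cohort 2 alone as reference**

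With an assumed fraction g of cohort 2 being novel product at 3.0, the observed ratio is 3 / (1 + 2g):

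- g = 10%: 3/1.2 = 2.5
- g = 25%: 3/1.5 = 2.0
- g = 50%: 3/2.0 = 1.5

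**5. Mixed index cohort (Objectives reading)**

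Observed ratio = (1 − q) × Angeliq ratio + q × other ratio, for q = 10%, 25%, 50%:

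- Angeliq 3.0, others 1.0: 2.8, 2.5, 2.0
- Angeliq 1.0, others 3.0: 1.2, 1.5, 2.0

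The same ambiguity can hide an Angeliq signal or create one.

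**The case against.** The strongest reply is that the conflict is contingent and partly a matter of shorthand. Angeliq is the only novel product named, and Objectives says only potentially. If no other novel product is launched and enrolled, all sections describe the same cohorts. Design and Exposure data never name a novel product as a comparator; that follows only from their use of other. Study participants says formulations will be distinguished in the analysis, and the questionnaires collect brand names, at follow-up with dates of use, so an Angeliq-only contrast is feasible under either reading.

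The contingency stands and limits the severity. The rest does not remove the conflict. Distinguishing formulations assigns no product to a cohort, and the final analysis still compares the three main cohorts. Nor is this a detail lost in condensing, because the article does define the cohorts and does so inconsistently.

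Three stronger readings are tempting, and the documents do not support them:

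- **Bias is always toward 1.** Steps 3 and 5 show otherwise.
- **A true 3.0 would shrink to about 2.1 against the pooled comparators.** That needs about 20% of comparator time to be novel product (3/1.4 = 2.14). With a comparator share of at least 90%, this is about 18% of all observation or more (0.2 × 0.9), above the 10% assumed for the new product or products.
- **Assignment would be chosen after the data are seen.** Final analysis reports a detailed plan approved by the Advisory Committee in September 2004 and March 2005. It is not shown and may settle the assignment.

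**Conclusion.** The inconsistency is real and concerns the index and reference groups of the main comparison. Taken literally, Design, Exposure data and Final analysis together put products under surveillance into the reference group, against the stated contrast of new with established products.

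The consequence is conditional on another novel product being launched and enrolled. With all novel products at 3.0 and a 10% total share, the distortion against the pooled comparators is modest: a true 3.0 appears as about 2.7 to 2.9. It is larger if novel products concentrate in cohort 2 (2.5 at 10%, 2.0 at 25%) or if the index cohort is mixed. These shares are assumptions. Because ratios under 2.0 to 3.0 are to be called inconclusive, even the smaller shifts fall inside that band if its upper end is applied. At a ratio of 3.0 the harm is to bias and interpretation more than to power. Severity: moderate.

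**What to change.** - Give one cohort definition and use it in Background, Objectives, Design, Exposure data and Study size estimation, including whether the 10% refers to Angeliq or to all novel products.
- Restrict both comparator cohorts to products with established estrogens and progestagens, using a brand-to-cohort list fixed before any outcome comparison.
- Assign every other novel oral combined product, continuous-combined or not, to the novel side, and state how its users enter the center-level selection.
- Report the Angeliq contrast separately from any pooled novel-product contrast. A separate index cohort for every novel product is a possible design preference, but it is not needed to remove the contradiction.

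The cost is wording and a brand list, since brand names are already collected. Comparator women-years fall somewhat if other novel products are enrolled: in step 3, by 1.1% to 5.3% of the comparator time.

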### Design

Prospective, controlled cohort study of users of HRT with follow-up: one cohort of women starting with or switching to Angeliq^®^, one comparison cohort of other oral continuous-combined HRT users (starter or switcher), and a third cohort of all other marketed oral HRTs (starter or switcher).

### Study participants

The combined cohorts will include at least 30,000 women aged 40 or more years who started or switched to an oral HRT at the time of inclusion in the study.

Following an indication for hormone replacement therapy, the prescribing physicians will determine whether women are eligible to participate. The primary objective is to accrue women in early or late menopause. For some women, postmenopausal status will be unclear and they will be described as "perimenopausal". Perimenopausal women who are prescribed oral HRTs will be included in this study. There will be stratified analyses for women who were clearly menopausal and women for whom this was not clear for various reasons (e.g., treatment). Women newly taking a herbal menopausal remedy are not eligible for inclusion. Different HRT formulations will be distinguished during the analysis.

Additional study inclusion criteria will not be given. Rather study inclusion will be the decision of the individual prescribing physician after explaining the benefits and risks to the woman. This approach supports the aim of the active surveillance study, which is to reflect drug use under real-life conditions. Evaluation of data for certain subgroups such as "HRT switchers" and "perimenopausal women" can be performed later in the analysis. Subgroup analyses for certain age groups will also be considered.

The women will be asked if they are willing to participate after being fully informed about the study. Women who start with hormone replacement or switch from another HRT can be included. For each woman who receives a prescription for the new HRT at a given center, one woman who receives an HRT prescription from each of the other two groups will be selected.

Women who do not consent to a long-term follow-up study, who have contraindications for HRT, or who have language difficulties, will not be eligible.

### Information gathered

#### Exposure data

Exposure is defined - for this surveillance study - as new use of any oral HRT. This includes women who are first time users (starters) or those who switch to a new brand. The exposure group of particular interest is the group using Angeliq^®^, and two other exposure groups (other oral continuous-combined HRT products and all other oral HRT products) have been defined as comparators (see above). Herbal menopausal drugs and SERMS will not be included in the main analysis.

#### Confounding and effect-modifying factors

Factors considered as confounders, effect modifiers, or adjustment variables will include the following: age, smoking, hypertension, increased blood lipids, treated diabetes mellitus, body mass index, cardiovascular diseases (angina pectoris, myocardial infarction, stroke/TIA, venous thromboembolism), and family history of premature cardiovascular events (MI and stroke). If other potential confounders are identified in the analyses they will be adjusted for as appropriate.

*Outcomes: *The outcomes of particular interest are: cardiovascular mortality, incidence rates of myocardial infarction, stroke, and venous thromboembolism.

The relevant information will be gathered by means of a short self-administered questionnaire to be completed by the participating women (including consultation with their physicians if necessary). The baseline questionnaire will contain questions related to the state of health, risk factors (medical history), and confounders, including drug use. The follow-up assessment of the combined cohort will be done after 6 months, 12 months, and then on an annual basis by means of a questionnaire mailed to the cohort members. This follow-up questionnaire concentrates on experience with the newly prescribed HRT. The study will end when the last woman in the study completes the first year of follow-up and the average follow-up has extended for at least three years.

The questionnaires document the following information:

• Baseline: ID number; birthday; date of last menstrual bleeding; artificial menopause (operation); parity/births (number); OC use, age at start and stop, duration of OC use; any HRT use, how many different brands, duration of HRT, how many switches among brands, date of HRT cessation, name of last brand, name of current prescription; smoking status (current, former, never), number of cigarettes now and before cessation, date of cessation; medical history of relevant diseases such as myocardial infarction, arrhythmias (confirmed by ECG), stroke, pulmonary embolism, deep venous thrombosis, varicose veins, fractures, any cancer; family history of myocardial infarction or stroke, VTE, breast cancer; regular use of medicaments (specify); recent blood pressure reading, height/weight.

• Follow-up: ID number; occurrence of new conditions after last contact such as myocardial infarction, stroke, venous thromboembolism; fractures (specify); any cancer (specify), any other severe health problems (specify); hospitalizations (specify); all brand names of HRTs used since last contact, including dates; regular use of medicaments (specify); changes in smoking status; weight/height; other relevant information; personal changes; name of treating physician/hospital to enable contact (if an AE/SAE has occurred).

If the women report serious adverse events (SAEs), the investigators will discuss these events with the women and the treating physician(s). Serious adverse events will be reported to the respective manufacturer regardless of whether the attending physician already reported the event through official channels in the respective country. Necessary steps will be taken to facilitate rapid reporting in the event of unexpected SAEs.

### Data handling

The questionnaire will first be checked manually for completeness and consistency at the coordinating center. In case of missing data, contradictions, questions, or obvious errors, the participants will be contacted for clarification. After completion of manual checks, the forms will be entered into an electronic database designed to meet the specific needs of a long-term cohort study.

Non-respondents will be sent a second, and if necessary, a third mailing. The names and addresses of the remaining non-respondents will then be checked in compliance with national laws to obtain information about possible changes. For any remaining non-respondents, attempts at tracing will be made using the contact persons named at the time of last contact.

To further maximize follow-up after the baseline survey, the women will be asked at every contact to announce any personal changes, e.g. telephone numbers. If a woman reports any of a specified list of medical outcomes, a follow-up form will be sent to request consent to inspect the medical records. Information on the name of the relevant physician, hospital, etc. will be recorded in order to gain access to the records.

